### Sample size

We plan to include 80 municipalities. We estimate that there are an average of 3.68 practices per municipality and 2.97 GPs per practice (10.93 GPs per municipality), based on data from Statistics Norway and the Norwegian Medical Association. We conducted power calculations for the primary outcome (adherence to recommendations) assuming an alpha of 0.05 (risk of type I error), the ability to detect a minimum difference of 0.05 between the control group and the intervention group regarding GPs’ adherence to the recommendations (the primary outcome: the proportion of recommendations that are implemented by the general practitioners), a standard deviation of 0.17 and an intra-class correlation coefficient (ICC) of 0.02. We assumed that 40%, 50% or 60% of GPs will consent to data collection in samples with 60, 70 or 80 municipalities, respectively. Based on a previous study in which we randomised municipalities, we estimate that the ICC will be less than 0.03 [39]. Based on the assumption that most GPs currently adhere on average to 4 or less of the 7 or 8 recommendations per patient, and a pilot survey of 11 GPs, we estimate that the standard deviation most likely will be less than 0.2.

Based on these assumptions, our calculations indicate that the power to detect a minimum difference in adherence to the recommendations among GPs of 0.05 (scale 0 to 1) in a sample of 80 municipalities is 0.80 provided the standard deviation is 0.17, the ICC 0.02 and 50% of GPs consent to data collection. With 80 municipalities, 437 GPs should be included in the study and this would provide data for at most 2,622 patients. The detailed results of the power calculations are provided in Additional file 1: Appendix D.

### Recruitment

All 80 selected municipalities will be included in the study. We will seek consent from all GPs in the 80 municipalities, prior to data collection, after the intervention has been delivered. Participation in the intervention is optional; for example, GPs can elect to participate in an outreach visit or not. After the intervention, GPs in both the intervention and control groups will be invited to participate in the study as part of a free module-based course for continuing medical education on ‘Depression in the elderly’; however, for GPs in the control group this activity will start with data collection after the intervention. For this activity they will get credits for obtaining or renewing their speciality in general practice. During the course, we will collect data through an individual audit and feedback session. We will offer GPs who do not want to participate in the course the option of the audit and feedback session on its own. Patients will receive information about the study and a questionnaire. They will consent to participation by replying to the questionnaire and give informed consent.

#### Randomisation

A statistical consultant will randomise the municipalities. Computer-generated random numbers will be assigned to all 80 municipalities, without modifications in the group to which a municipality is randomly allocated. The municipalities will be divided into four strata based on information from Statistics Norway:

1. Municipalities with city status or a large population (>25,000 inhabitants)

2. Municipalities with a small population (≤25,000 inhabitants)

1. Municipalities with a high proportion of inhabitants aged 80 or older (>5%)

2. Municipalities with a low proportion of inhabitants aged 80 or older (≤5%)

From a representative selection of 80 municipalities from southern, eastern and northern Norway, we identified 19 municipalities with city status and/or a population larger than 25,000, 61 municipalities with a population ≤25,000, 46 municipalities with more than 5% of people over 80, and 34 municipalities with ≤5% of people 80 years or older (Additional file 1: Appendix C).

### Blinding

Blinding of the participants and the researchers regarding the intervention will not be possible. We will analyse and interpret the results without knowing the allocation. The interventions will be implemented before we contact the GPs to ask them to collect data for the study.

### Data collection

At the start of the study we collected the following baseline data for each municipality:

• Number of inhabitants, number of elderly patients (65+), the proportion of inhabitants aged over 80 and the number of GPs (from Statistics Norway and the municipalities)

• Whether the municipality has collaborative care plans for elderly patients with depression, for adult patients with depression, or for adults with mental health problems including for elderly patients with depression (collected by questionnaire with telephone follow-up if needed). If so, we will obtain a copy for further analysis

• Written agreements for routines for referral within primary care and between primary care and specialist health care

• A plan for depression care managers

• A plan for collaboration with voluntary organisations

• Whether the municipality is a member of the ‘Centre for Development of Institutional and Home Care Services’ network.

• Whether the primary-care-based psychiatric nurse teams provide regular services to the elderly population (65+)

We will collect outcome data beginning three months after the delivery of the intervention. In both groups we will collect data for all eligible patients using GPs’ medical records, structured interviews with GPs, brief questionnaires mailed to patients and questionnaires mailed to each municipality (with telephone follow-up, if needed). We anticipate that treatment strategies provided to patients with depression may take up to three months to prove beneficial.

Prior to contact with GPs, we will send them a program that will extract and identify eligible patients from their medical records. We will contact each GP practice that has consented to participate by telephone and identify eligible patients in their electronic medical records using the algorithm described in Additional file 1: Appendix A and collect the following information using structured telephone interviews with each GP:

• Depression severity according to ICD-10 for six patients identified with depression

• GP’s adherence to recommendations (primary outcome measure)

• GP’s assessment of a patient’s improvement, as measured CGI-I (secondary outcome measure)

• GP’s awareness and knowledge of a collaborative care plan in the municipality

If the GP faces any technical problems using the electronic device, we will provide support to solve the problem and if needed visit the GP to collect data.

Based on previous studies [40,41] we anticipate that between 40% and 60% of GPs will consent to data collection. All GPs that consent to participate will be asked to mail a questionnaire to each of the six patients that have been identified. Patients will be asked to complete and return the questionnaire by mail. If a patient consents to participate in the study, but does not wish to complete the questionnaire, we will ask the patient to appoint a family member to answer on their behalf if possible. Alternatively the patient may choose to consent to being contacted and interviewed by telephone.

The following data will be collected from patients:

• The patient’s assessment of improvement for depression, anxiety, sleep problems, physical activity, problem-solving, social contact and loneliness (secondary outcome measures)

• Adherence to medication

Each patient, GP and municipality included in the study will receive a unique study ID, which is available to the research group. A list at each GP practice will couple the patient’s study ID and the patient’s national ID number. We will use the patient ID numbers generated by the GPs’ electronic medical records systems. It will be possible for GPs to identify patients using these numbers, but the investigators will not have access to information identifying the patients, unless they first return a mailed consent form with the questionnaire. All communication (for example, letters) with patients will otherwise be through the patients’ GP.

We will collect the following descriptive data from GPs: age, sex, years of clinical experience as a GP, whether they are a specialist in primary-care medicine, competency in using CBT (collected during the structured interviews) and the number of elderly patients (65+) on the patient list.

A schematic presentation of participant timeline and time schedule for data collection is presented in Additional file 1: Appendix E.

### Statistical methods

The primary outcome of interest for our analysis is the mean adherence rate per GP (based on six patients). We will assess the number of recommendations that were followed with regard to the severity of depression, and we will calculate an overall mean for adherence across disease severity for each GP. For mild and moderate depression there are seven recommendations and for severe depression there are two recommendations; these will be assessed by interviewing the GP, who will have access to patients’ medical records during the interview. The analysis will be performed as an intention-to-treat analysis; we count all GPs in the group to which they were assigned, regardless of whether they received the intervention or not.

All analyses will be performed in SAS version 9.2 (SAS Institute Inc.) using PROC GLIMMIX with random effects for municipality and practice to account for the clustered nature of the data. Continuous data will be analysed assuming that the data follows a normal distribution (linear regression) and dichotomous data will analysed using the binomial distribution (logistic regression). In the initial analyses only the allocation to intervention or control will be included as an independent variable in the analysis (Intervention = YES/NO).

The following factors and variables are assumed to be effect modifiers: whether the municipality already has a collaborative plan (may improve adherence), whether access to cognitive behavioural therapy is poor (may reduce adherence), whether municipalities belong to the ‘Centre for Development of Institutional and Home Care Services’ network (may improve adherence) and whether GP has many elderly patients on the list (may improve adherence).

Each of the pre-specified effect modifiers will be separately included as independent variables (alongside allocation to intervention or control) in the model. All the effect modifiers with *P* < 0.3 in the previous step will be included as independent variables in a final multivariate model.

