Each ‘yes’ scores 1, a score of 0 suggests no problem with medicine-taking and hence good compliance. The maximum of 4 for the four questions indicates major difficulties and suggests poor compliance.

We will assess whether the following items are present at the municipal level:

1. A collaborative care plan including a plan for elderly patients with depression (document)

2. An identifiable case manager

3. Agreed referral processes

4. Agreed communication processes within primary health-care services

5. Agreed communication processes between primary health-care and specialist health-care services

6. A list of voluntary organisations

7. Awareness of the collaborative care plan (proportion of GPs who are aware of the plan)

8. Knowledge of the collaborative care plan (proportion of GPs who can answer a factual question about the content of the plan)

We will collect data for the first six items above by questionnaires sent to municipality representatives. We will collect data for the last two items during practice visits at the end of the study.

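### The random-effects model set for all analyses is not identifiable for the six municipal questionnaire outcomes, and most of the related baseline data have no stated role

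*Protocol article*

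**What the plan says.** Statistical methods sets one modelling framework: "All analyses will be performed in SAS version 9.2 (SAS Institute Inc.) using PROC GLIMMIX with random effects for municipality and practice". For yes/no outcomes it adds that "dichotomous data will analysed using the binomial distribution (logistic regression". It names no exception for outcomes measured on the municipality itself.

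Secondary outcomes ends with eight municipal items, introduced by "We will assess whether the following items are present at the municipal level". The first six are a care plan, a case manager, referral processes, two kinds of communication process, and a list of voluntary organisations. Their source is stated: "We will collect data for the first six items above by questionnaires sent to municipality representatives". Items 7 and 8 differ in kind, for example "Awareness of the collaborative care plan (proportion of GPs who are aware of the plan", and are collected from GPs.

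On covariates, Statistical methods says: "In the initial analyses only the allocation to intervention or control will be included as an independent variable in the analysis (Intervention = YES/NO". A second step adds assumed effect modifiers one at a time beside allocation, and those with P < 0.3 go into a final model. One of them is "whether the municipality already has a collaborative plan (may improve adherence".

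Data collection lists baseline information on each municipality. It begins with "Whether the municipality has collaborative care plans for elderly patients with depression" and also covers written referral agreements, a plan for care managers and a plan for working with voluntary organisations.

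**The concern.** A random intercept for municipality describes how observations within a municipality resemble each other. Items 1 to 6 have one observation per municipality, so there is no within-municipality resemblance to estimate. A practice effect has no data at all, because the questionnaire answer is not tied to a practice. Followed literally, the stated model may return a zero variance, fail to converge, or give an odds ratio that the data do not determine.

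The second part concerns efficiency. The trial records at baseline several features close to these outcomes, but the initial model uses none of them. A municipality that already has the feature has little room to show an effect, so mixing such municipalities with the rest dilutes the contrast.

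The first three recommendations are delivered at municipal level, which is one of the protocol's reasons for randomising municipalities. Items 1 to 6 are the direct evidence on whether that part was taken up.

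**Working it through.** **The plan's own figure.** The article gives no power figure for the municipal outcomes. Its sample size concerns GPs and reproduces: 80 × 3.68 × 2.97 × 0.5 = 437.2, stated as 437 GPs, and 437 × 6 = 2,622 patients. Those numbers do not apply to items 1 to 6, where at most 80 values exist per item.

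**Identifiability.** Let y be the single yes/no value of a municipality in arm x (0 or 1), with municipality SD σ on the log-odds scale. The probability of a yes is p(x) = ∫ expit(β0 + β1·x + σz) φ(z) dz. With one y per municipality, the likelihood depends on β0, β1 and σ only through p(0) and p(1). For any σ, some β0 and β1 reproduce the observed proportions exactly, so the profile likelihood for σ is flat.

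Illustration with assumed data, 6/40 control and 16/40 intervention (proportions 0.15 and 0.40):

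- log L = 6 ln 0.15 + 34 ln 0.85 + 16 ln 0.40 + 24 ln 0.60 = -11.383 - 5.526 - 14.661 - 12.260 = -43.83
- odds ratio at σ = 0: (16/24)/(6/34) = 3.78

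| Assumed σ | Maximised log-likelihood | Conditional odds ratio |
|---|---|---|
| 0 | -43.82883 | 3.78 |
| 0.5 | -43.82883 | 4.02 |
| 1 | -43.82883 | 4.75 |
| 2 | -43.82883 | 8.04 |
| 3 | -43.82883 | 15.34 |
| 5 | -43.82883 | 64.14 |

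The σ = 0 row is ordinary logistic regression.

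**Baseline and outcome items side by side.**

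| Municipal outcome | Baseline counterpart | Match | Stated role in analysis |
|---|---|---|---|
| 1 Care plan | Existing care plans | Close | Second step only, justified by adherence |
| 2 Identifiable case manager | Plan for care managers | Approximate | None |
| 3 Referral processes | Written referral agreements | Close | None |
| 4, 5 Communication processes | No clear counterpart | None | None |
| 6 List of voluntary organisations | Plan for collaboration with them | Approximate | None |

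**Size of the efficiency gain.** All rates are assumptions: 40 v 40 municipalities, new adoption 10% v 35% among those without the item, two-sided 0.05. A pooled two-proportion z test is compared with a Mantel-Haenszel test stratified by baseline status, by simulation. As an example of the dilution, with 30% having the item at baseline and 95% of them still having it at follow-up, the overall rates are 0.3 × 0.95 + 0.7 × 0.10 = 0.355 and 0.3 × 0.95 + 0.7 × 0.35 = 0.53. The difference is 0.175, against 0.25 among municipalities without the item.

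| Have item at baseline | Still have it at follow-up | Power unadjusted | Power stratified |
|---|---|---|---|
| 0% | not applicable | 0.79 | 0.79 |
| 2% | 95% | 0.75 | 0.78 |
| 5% | 95% | 0.70 | 0.76 |
| 10% | 95% | 0.60 | 0.73 |
| 30% | 95% | 0.37 | 0.58 |
| 50% | 95% | 0.21 | 0.39 |
| 30% | 70% | 0.37 | 0.45 |
| 50% | 70% | 0.22 | 0.24 |

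The 70% rows stand for a baseline item that only roughly matches the outcome.

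**The case against.** The strongest reply on the model is that the random effects are there to handle clustering. Where there is none, a sensible analyst would drop them and fit the ordinary logistic regression that the same section names. Software that returns a zero variance lands on that answer anyway. The article also condenses a fuller plan that may make the exception. This is fair as to consequence, and it rules out saying that the model simply cannot be run. It does not remove the point, because the text prescribes the random effects for every analysis, and what comes out for items 1 to 6 would then depend on software behaviour rather than on the data.

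A reader might also infer that all municipal outcomes are affected. They are not: items 7 and 8 rest on several GPs per municipality, and random effects suit them.

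A reader might infer that the baseline data are ignored altogether. That is too broad. Existing collaborative-plan status is a pre-specified second-step covariate, although its rationale is GP adherence and it is not named as adjustment for the plan outcome.

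On efficiency, the objection largely stands. An allocation-only comparison of randomised groups is valid, and its standard error covers chance imbalance. The Usual care section also suggests low baseline prevalence for two items: the authors say that elderly-specific depression plans are absent and that, to their knowledge, the case-manager service has not been systematically implemented. At such rates the gain is close to nil. The same section does describe some existing general mental-health plans, regional collaboration agreements and volunteer involvement, so prevalence need not be near zero for every item.

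**Conclusion.** The point holds for six of the eight municipal secondary outcomes. For items 1 to 6 the prescribed random-effects model is not identifiable. That follows from the data structure and needs no assumed rates; the 6/40 v 16/40 data only illustrate it. The primary analysis is untouched.

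The baseline part is a matter of efficiency, not validity. Referral agreements, the care-manager plan and the voluntary-organisation plan are collected without a stated analytic role, and care-plan status enters only in the second step. The gain from using them runs from none at 0% baseline prevalence, through 0.60 v 0.73 at 10%, to 0.37 v 0.58 at 30% with 95% retention, and it shrinks to 0.37 v 0.45 at 30% with 70% retention. These figures rest on assumed adoption and retention rates and an assumed 40:40 split. They do not support a general claim that much power is lost.

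**What to change.** In Statistical methods, exempt municipal items 1 to 6 from the random effects. Analyse each with one row per municipality by logistic regression, exact or penalised if events are sparse. Adjust for the two stratification factors (city status or population size, and proportion aged 80 or older) and for the matching baseline item where one exists: closely for care plan and referral, approximately for case manager and voluntary organisations, and none for the two communication items. Keep the random effects for items 7 and 8 and for the GP- and patient-level outcomes.

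The cost is a few sentences of analysis wording. The baseline items are already part of the data collection, so no new data are needed.

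### Municipalities are randomised within four strata, but no analysis model includes the strata: a small, mainly conservative loss of precision that is cheap to avoid

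*Protocol article*

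**What the plan says.** Under Randomisation, the protocol article says: "The municipalities will be divided into four strata based on information from Statistics Norway". Two binary factors follow: city status or more than 25,000 inhabitants against the rest, and more than 5% of inhabitants aged 80 or older against the rest. Only the margins are given. On the first factor "we identified 19 municipalities with city status and/or a population larger than 25,000", leaving 61 smaller ones; on the second the split is 46 and 34.

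Under Statistical methods, the models are fitted "using PROC GLIMMIX with random effects for municipality and practice to account for the clustered nature of the data". The fixed part is settled as follows: "In the initial analyses only the allocation to intervention or control will be included as an independent variable in the analysis". Four effect modifiers are then named: an existing collaborative plan, poor access to cognitive behavioural therapy, membership of a development-centre network, and many elderly patients on the GP's list. The next step reads: "Each of the pre-specified effect modifiers will be separately included as independent variables (alongside allocation to intervention or control) in the model". Those with P < 0.3 "in the previous step will be included as independent variables in a final multivariate model". Neither stratification factor is among the four.

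The information needed is at hand. The baseline data under Data collection include "Number of inhabitants, number of elderly patients (65+), the proportion of inhabitants aged over 80 and the number of GPs".

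**The concern.** The design and the analysis do not match. Balanced allocation within strata removes between-stratum differences from the sampling variance of the treatment effect. A mixed model with allocation alone does not know this. It leaves those differences in the municipality random effect, and so in the reported standard error. The interval is then wider than the design warrants, and the test runs below its nominal 5%.

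A second consideration is particular to this trial. Stratification acts on the number of municipalities, whereas the analysed units are GPs who consent after the intervention has been delivered (Recruitment), with 40% to 60% expected to do so (Data collection). The stratum mix of analysed GPs may therefore differ between arms even when municipalities are balanced, and an allocation-only model does not adjust for that.

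At stake is some power, which matters most if the result is borderline or null. The validity of a positive finding is not at stake.

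This is not a detail that the article leaves to a fuller document. It fixes the initial model and lists what may enter later.

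**Working it through.** **Inputs from Sample size:** 80 municipalities; 10.93 GPs per municipality; 50% consent; difference 0.05; SD 0.17; ICC 0.02 (expected below 0.03); alpha 0.05. **Assumptions, not in the article:** two-sided test, 1:1 allocation, normal approximation, no separate practice-level variance, R² (the share of between-municipality variance explained by the strata) and CV (coefficient of variation of cluster size).

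**The plan's own figures.** GPs per municipality m = 10.93 × 0.5 = 5.465. Total 80 × 5.465 = 437.2, matching the stated 437; 437 × 6 = 2,622 patients, also as stated. Design effect = 1 + 4.465 × 0.02 = 1.0893. SE = 0.17 × √(2 × 1.0893/218.6) = 0.01697. Power = Φ(0.05/0.01697 − 1.96) = Φ(0.986) = 0.838, or 0.829 with a t distribution on 78 degrees of freedom. The stated power is 0.80. A CV of about 1 gives 0.802, so unequal cluster sizes could explain the gap. The detailed calculation is in Appendix D, which is not shown, and 0.80 is the cautious side, so no error is claimed there.

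**Effect of leaving the strata out, if allocation is balanced within strata.** The true variance factor is

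F(R²) = (1 − ICC) + m(1 + CV²) × ICC × (1 − R²).

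The allocation-only model reports the SE from F(0); the true SE uses F(R²). Then:

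- actual alpha = 2[1 − Φ(1.96 × SE reported/SE true)]
- unadjusted power = Φ((0.05 − 1.96 × SE reported)/SE true)
- adjusted power = Φ(0.05/SE true − 1.96)

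Worked for ICC 0.02, CV 0, R² = 1: F(0) = 0.98 + 0.1093 = 1.0893 and F(1) = 0.98, so the SEs are 0.01697 and 0.01610, a ratio of 1.054. Unadjusted power = Φ((0.05 − 0.03326)/0.01610) = Φ(1.04) = 0.851. Adjusted power = Φ(3.106 − 1.96) = 0.874.

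| ICC | CV | R² | Reported SE too large by | Actual alpha | Power unadjusted | Power adjusted |
|---|---|---|---|---|---|---|
| 0.02 | 0 | 0.25 | 1.3% | 0.047 | 0.841 | 0.847 |
| 0.02 | 0 | 0.5 | 2.6% | 0.044 | 0.844 | 0.856 |
| 0.02 | 0 | 1 | 5.4% | 0.039 | 0.851 | 0.874 |
| 0.02 | 1 | 0.5 | 4.9% | 0.040 | 0.813 | 0.838 |
| 0.02 | 1 | 1 | 10.6% | 0.030 | 0.826 | 0.874 |
| 0.03 | 0 | 0.5 | 3.8% | 0.042 | 0.832 | 0.850 |
| 0.03 | 0 | 1 | 8.1% | 0.034 | 0.842 | 0.877 |

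At ICC 0.02 the loss is 0.6 to 2.3 points with equal clusters and reaches 4.8 points at CV 1. The extreme corner of ICC 0.03, CV 1 and R² = 1 gives 0.804 against 0.877. R² = 1 is a bound: it requires two binary factors to explain all variation between municipalities.

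**The case against.** Several points can fairly be made for the plan.

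*The error is on the safe side.* This stands. Alpha falls below 0.05 and the linear-model estimate is unbiased. With equal clusters at ICC 0.02, the allocation-only test stays above the planned power of 0.80.

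*Balance is not lost.* This also stands. A reader might infer that leaving out the strata throws away the balance that stratification achieved. It does not: the balance sits in the design and in the point estimate. Only the credit for it in the standard error is missing.

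*Balanced allocation within strata is not stated.* The Randomisation section describes computer-generated numbers for all 80 municipalities and mentions neither blocking nor a fixed ratio within strata. If allocation within strata is unrestricted, the reported standard error is not too large in the way described. Adjustment would still add precision: at the R² = 1 bound with equal clusters the SE would go from 0.0170 towards 0.0161, less a small loss for chance imbalance. So this weakens the mechanism but not the case for adjusting.

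*The large municipalities may not dominate.* A reader might infer that the 19 large municipalities supply most of the GPs. That is plausible, but the article gives only an average per municipality and no GP counts by stratum. Stratum terms would correct for a differing stratum mix among analysed GPs; they would not cure selective consent within strata.

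*Stratum terms can do harm in small models.* This stands for the municipality-level yes/no outcomes, with at most 80 observations. From the margins, the cell of large municipalities with a high share aged 80 or older could hold anything from 0 to 19. The objection does not reach the GP-level linear model with about 437 GPs.

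**Conclusion.** The mismatch is real and stated in the article: the strata used to randomise enter no analysis model. Its consequence is modest. At ICC 0.02 with equal clusters, about 0.6 to 1.2 points of power are lost if the strata explain 25% to 50% of between-municipality variance, and 2.3 points at most. About 5 points is possible at a cluster-size CV near 1. These sizes rest on balanced allocation within strata and on assumed values of R² and CV, none of which the article gives.

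A reader might set the recomputed 0.838 against 0.874 and conclude that 3.6 points are lost. Under balanced stratified allocation that comparison mixes two situations: 0.838 is the power when the strata explain nothing, 0.874 when they explain everything. In the latter case the unadjusted test already has 0.851. Nor do the documents support reading this as bias or as an inflated false-positive rate. It is an efficiency point worth correcting because the correction is nearly free.

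**What to change.** In Statistical methods, include the two binary stratification factors as fixed effects, alongside allocation, in the GP-level linear model for mean adherence. Designate that model as the primary analysis and keep the allocation-only model as a sensitivity analysis. The product of the two factors need not be required, and stratum terms should not be imposed on the municipality-level logistic models, where cells may be sparse.

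The cost is one line of text and two degrees of freedom (78 to 76 at municipality level). No new data are needed, since each municipality's stratum is known from randomisation. The change should be made before outcome data are analysed.

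### GPs are recruited unblinded after the intervention, yet the collected GP characteristics (age, sex, experience, specialist status) enter no model that could partly correct for selective consent

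*Protocol article*

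**What the plan says.** Under Statistical methods, the outcome for analysis is one mean adherence rate per GP, from up to six patients, with random effects for municipality and practice. In the initial analyses "only the allocation to intervention or control will be included as an independent variable in the analysis". We read this as the primary comparison.

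Four pre-specified factors are then added one at a time beside allocation: an existing collaborative plan, poor access to CBT, membership of a development-centre network, and many elderly patients on the GP's list. Those with P < 0.3 go into a final multivariate model.

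Under Data collection, the article lists GP data described as descriptive: "age, sex, years of clinical experience as a GP, whether they are a specialist in primary-care medicine", together with competency in CBT and the number of patients aged 65 or over. Apart from list size, none of the GP traits named in the quote appears in any modelling step.

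Recruitment and Ethics place GP consent after the intervention has been delivered. Blinding says that participants and researchers cannot be blinded to the intervention. Data collection anticipates consent from 40% to 60% of GPs.

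**The concern.** Municipalities are randomised, but the units that carry the outcome are GPs who decide afterwards whether to supply data. In the intervention arm they decide after exposure to the package; in the control arm they have had no contact with it. The invitation comes with a course that earns credits towards obtaining or renewing the GP specialty, so its appeal may vary with career stage and specialist status. For control GPs this activity begins only with data collection. The two arms thus meet the invitation in different circumstances, and different kinds of GP may accept.

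The intention-to-treat rule keeps consenting GPs in their assigned arm but cannot bring back those who decline. If consent is selective on a trait that also predicts adherence, the allocation-only estimate carries that difference. The later models could absorb it only through list size, and only if list size passes the P < 0.3 screen. A second and smaller stake is precision: covariates that predict the GP score would reduce its residual variance.

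**Working it through.** **Inputs from Sample size.**

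- Significance level: "assuming an alpha of 0.05 (risk of type I error".
- Target effect: "the ability to detect a minimum difference of 0.05 between the control group and the intervention group".
- Spread and clustering: "a standard deviation of 0.17 and an intra-class correlation coefficient (ICC) of 0.02".
- Cluster size before consent: "3.68 practices per municipality and 2.97 GPs per practice (10.93 GPs per municipality".
- Power claimed for 80 municipalities: "is 0.80 provided the standard deviation is 0.17, the ICC 0.02 and 50% of GPs consent to data collection".

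Two-sided alpha and 1:1 allocation are our assumptions, since the article states neither.

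**Reproducing the plan.** GPs: 80 × 10.93 × 0.5 = 437.2, which agrees with the stated 437.

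Power = Φ(0.05/SE − 1.96), with SE = 0.17 × √(4 × DE/437).

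- Equal clusters of consenting GPs: m = 437/80 = 5.46, DE = 1 + 4.46 × 0.02 = 1.089, SE = 0.0170, power 0.838.
- m = 10.93 (all GPs): DE = 1 + 9.93 × 0.02 = 1.199, power 0.802. A cluster-size coefficient of variation of 1.0 (assumed) at m = 5.46 gives the same.

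The stated 0.80 is therefore reproduced with a design effect of about 1.20. Both bases are carried forward.

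**Precision.** Let R² be the share of the variance of the GP score explained by the added covariates, assumed to act equally within and between municipalities. The SE is then multiplied by √(1 − R²). A power of 0.80 corresponds to 0.05/SE = 1.960 + 0.842 = 2.802, so

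Power = Φ(2.802/√(1 − R²) − 1.96).

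The documents give no R²; the range is assumed.

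| R² | SE ratio | Equivalent GPs, 437/(1 − R²) | Power from stated 0.80 | Power from 0.838 |
|---|---|---|---|---|
| 0 | 1.000 | 437 | 0.800 | 0.838 |
| 0.02 | 0.990 | 446 | 0.808 | 0.845 |
| 0.05 | 0.975 | 460 | 0.820 | 0.856 |
| 0.10 | 0.949 | 486 | 0.840 | 0.874 |

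On the SD, the authors say only that "we estimate that the standard deviation most likely will be less than 0.2". At 0.20 the stated base becomes Φ(2.802 × 0.17/0.20 − 1.96) = Φ(0.42) ≈ 0.66, and R² = 0.10 would lift it to about 0.71.

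**Selective consent.** Bias = (difference between arms in the share of GPs with a trait) × (effect of the trait on adherence). Both inputs are assumed.

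- 10 points × 0.05 = 0.005, which is 10% of the 0.05 target.
- 20 points × 0.10 = 0.02, which is 40% of the target.

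For comparison, the chance SE of such a difference for a trait held by half the GPs, with the same design effect of 1.089 assumed, is √(0.25 × 4 × 1.089/437) = 0.050, or 5 points.

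**The case against.** The strongest reply is that an allocation-only mixed model is a valid primary analysis of a cluster randomised trial, and that collecting GP traits purely for description is legitimate. Both points stand. A reader might infer that the plan contradicts itself by collecting these variables without modelling them; it does not.

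A reader might also infer that the plan makes no adjustment at all. That is wrong too: the restriction to allocation applies to the initial analyses, and four factors are entered later as independent variables, one of them at GP level.

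It is tempting to say that chance imbalance between the GP groups is left uncorrected and so biases the result. It does not; the standard error of the unadjusted comparison already allows for it. Only selective consent biases the estimate. Adjusting for a few demographic traits corrects that at best in part, because motives such as interest in the topic are not measured by them.

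On precision, nothing in the article shows that these traits predict adherence, and they are not among the factors the authors expect to matter. Part of the GP score is also noise that GP traits cannot explain. With 42 independent items (six patients × seven questions) at a probability of 0.5 (assumed), that part is 0.25/42 = 0.006, about 21% of 0.17² = 0.0289. Explaining 5% of the remaining 79% means R² ≈ 0.04 and power of about 0.816, not 0.820.

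Finally, specialist status is not strictly fixed, because the course credits count towards it. This is met by taking the status held at randomisation.

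What remains is that the covariate set of the initial model is stated, not left open, and that it ignores already collected traits where GP recruitment follows an unblinded intervention.

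**Conclusion.** The point holds as a modest improvement to a stated analysis. It is not an error that invalidates the analysis. The GP groups compared are formed after allocation, from an expected 40% to 60% of those eligible, and no model described uses GP age, sex, experience or specialist status.

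Neither the size of any bias nor the gain in precision can be fixed from the documents. The bias figures of 0.005 and 0.02 are illustrations. The power gain runs from nothing at R² = 0 to about 4 points at R² = 0.10, so a firm claim that the plan gives up precision is not supported. Nor would the adjusted model remove selection bias; it addresses only the part carried by the measured traits.

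The argument for acting is that the data are already being collected, and that a covariate set chosen before the outcomes are seen is more credible than one chosen afterwards.

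**What to change.** - Pre-specify a model with allocation plus GP age (or years of experience, not both), sex and specialist status as held at randomisation, with the same random effects for municipality and practice.
- Report the allocation-only model alongside.
- Show by arm the number of GPs invited, the consent rate, and the characteristics of consenting GPs.
- Leave CBT competency out of the model. It is recorded after the intervention, which offers information on CBT training and can therefore change it.
- State that the adjusted model addresses selective consent only through measured traits.

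The cost is analysis-plan wording, plus asking that specialist status refer to the randomisation date. Downsides: a simple rule is needed for the few GPs with a missing characteristic, and there is little gain if the covariates prove weak.
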